### 12.2.4 ELTS score

A recent score developed for long-term outcome of imatinib-treated patients is the EUTOS long-term survival score (ELTS score) . As with the other three scores, score calculation should be based on clinical and laboratory parameters at diagnosis, prior to any CML-specific therapy including other than TKI. Its calculation can be performed via [http://www.leukemia-net.org/content/leukemias/cml/elts\\_score/index\\_eng.html](http://www.leukemia-net.org/content/leukemias/cml/elts_score/index_eng.html).

### 12.2.5 Medical and pre-treatment history

The medical and pre-treatment history will be assessed only once at Screening and will include: previous and ongoing clinically significant disorders.

### 12.2.6 Physical Examination / Vital Signs / Body Temperature

At each visit a complete physical examination will be performed. Moreover the blood pressure (systolic and diastolic), pulse rate and body temperature will be measured as scheduled in Table 1 and Table 2.

### 12.2.7 ECOG Performance Status

The performance status of the patients will be evaluated (Table 1 and Table 2) according to the ECOG performance status: ECOG = Eastern Cooperative Oncology Group.

**ECOG Performance Status Criteria**

| Grade | Criteria and Description According to ECOG                                                                                                                 |
|-------|------------------------------------------------------------------------------------------------------------------------------------------------------------|
| 0     | Fully active, able to carry on all pre-disease performance without restriction                                                                             |
| 1     | Restricted in physically strenuous activity but ambulatory and able to carry out work of a light or sedentary nature (e.g., light house work, office work) |
| 2     | Ambulatory and capable of all self-care but unable to carry out any work activities. Up and about more than 50% of waking hours                            |
| 3     | Capable of only limited self-care; confined to bed or chair more than 50% of waking hours                                                                  |
| 4     | Completely disabled. Cannot carry on any self-care. Totally confined to bed or chair                                                                       |
| 5     | Dead                                                                                                                                                       |

**Table 7 ECOG Performance Status Criteria****12.2.8 Clinical Laboratory Evaluation**

Blood samples for safety evaluation (hematology, clinical chemistry, and coagulation parameters) will be collected as scheduled in Table 1 and Table 2. Determination of safety laboratory parameters will be performed at the central laboratories. Any abnormalities in any of the laboratory parameters will be judged in relation to the reference ranges from the laboratory and to the clinical relevance assessed by the investigator. The investigator will grade any clinically relevant parameter outside the normal range according to the NCI CTCAE (Version 4.03).

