### 4.2 Secondary endpoints

- RFS 13 months after randomization
- RFS 25 months after randomization
- Safety, tolerability and toxicity based on incidences of adverse events, serious adverse events, frequency of clinical laboratory tests by worst toxicity grade
- Quality of life (EORTC QLQ-C30 and EORTC-QLQ-CML24 questionnaires) The QoL assessment in this study is planned to gain information on the QoL of CML patients under stopping conditions. The data will be compared between the treatment groups and to QoL of normal population. Furthermore, results of the CML24 module should be shared with the EORTC group to complete the validation of this questionnaire
- Explore the value of  $95 \text{ CD86+ pDC} / 10^5$  lymphocytes at baseline (before TKI stop) as a predictor of TFR
- Overall survival (OS), defined as the time between the date of randomization and the date of death from any cause.
- Explore immunological and genetic biomarkers to study biology of TFR, and identify predictors IFN response (e.g. mRNA sequencing of whole blood or leukocyte subpopulations, PD-L1-, PD1-, CD62L- measurements by FACS on peripheral blood subsets, T-cell activation and exhaustion marker measurements, PR1-CTL assessment and cytokines).
- Evaluation of cytokines/chemokines (i.e., IL-6, IFN- $\alpha$ , IL 10, and others).
- Kinetics of BCR-ABL transcript level over time after TKI stop

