## 7 Blinding

This is an open-label assessor blinded study. Subjects and investigators will be not blinded to the treatment assignment. A placebo-controlled randomization was not considered meaningful, because flu-like side effects regularly occur and would make a blinded, placebo-controlled treatment futile.

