**12.2.8.1 Hematology**

Two (2) ml of blood will be placed in an ethylene diamine tetraacetic acid (EDTA) tube and the following parameters will be measured: hemoglobin, platelet count, leukocyte count, neutrophils.

The clinical significance of each hematology value exceeding the alert values presented in Table 8 should be assessed and should be recorded in the e-CRF. When a value is clinically significant, an AE should be recorded.

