## 16.6 Safety Variables

The following safety assessments are considered as safety endpoints:

- Safety profile of AOP2014 in terms of the incidence of AEs graded according to NCI CTC Version 4.03;
- Autoimmunity induced by AOP2014 in terms of ANA.

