### **Safety endpoints**

The safety analyses will be based on the safety population. Safety variables will be tabulated by treatment group and listings will be given.

Cumulative probabilities of the occurrence of adverse events will be calculated. Firstly, cumulative probabilities for the occurrence of any adverse event, secondly the occurrence of any adverse event of grade 3 or 4 will be plotted by cumulative incidence curves. Cumulative incidence curves will consider competing risks. One competing risk would be death without prior recording of any adverse event.

Using cumulative incidence curves, also probabilities for the observation of particular adverse events of interest are considered.

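### Worst-grade laboratory toxicity is a secondary safety endpoint (4.2), but the only grading rule (12.2.8) rests on the open-label investigator's view of clinical relevance, and the safety list in 16.6 omits the endpoint

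*Protocol*

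**What the plan says.** - **Endpoint.** Section 4.2, and the synopsis in the same terms, includes "frequency of clinical laboratory tests by worst toxicity grade" in the secondary endpoint on safety, tolerability and toxicity.
- **Grading rule.** Section 12.2.8 has the safety parameters measured at central laboratories. Abnormal results are judged against the laboratory's reference ranges "and to the clinical relevance assessed by the investigator". Then: "The investigator will grade any clinically relevant parameter outside the normal range according to the NCI CTCAE (Version 4.03").
- **Blinding.** Section 7: "Subjects and investigators will be not blinded to the treatment assignment".
- **Haematology alert values.** Table 8 in 12.2.8.1 sets limits for neutrophils, haemoglobin, leukocytes and platelets. The clinical significance of each value beyond its limit is to be assessed and documented in the e-CRF. "When a value is clinically significant, an AE should be recorded".
- **Safety endpoints in the statistical section.** Section 16.6 has two items: "Safety profile of AOP2014 in terms of the incidence of AEs graded according to NCI CTC Version 4.03" and "Autoimmunity induced by AOP2014 in terms of ANA".
- **Safety analysis.** Section 16.7: "Safety variables will be tabulated by treatment group and listings will be given". It also plans cumulative incidence curves for any adverse event and for adverse events of grade 3 or 4.

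**The concern.** A table of worst grade by arm is sound only if each patient's worst out-of-range value receives a grade. Under 12.2.8 as worded, a value outside the reference range that the investigator considers irrelevant has no stated route to a grade. The same numeric result could be graded in one patient and left ungraded in another, and the person deciding knows the arm.

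The protocol gives reasons why attention to laboratory values might differ between arms. Section 10.2 lists leukopenia and thrombocytopenia as very common with AOP2014 and liver enzyme increases as common. The dose-modification tables in 10.3.1.1 for neutrophils, platelets and transaminases apply to AOP2014 and so only to arm A. Patients may also enter with bilirubin, LDH, AST and ALT up to 2 × ULN (inclusion criterion 7), so whether a mildly raised value is relevant will be a real question.

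At stake is the usefulness of one descriptive safety table. Laboratory values are the safety data that depend least on opinion, and the stated rule brings opinion back in at the grading step.

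**Working it through.** The protocol states no figure on this point, so there is none to reproduce. The check is a comparison of its sections.

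1. **Does 4.2 need a grade that 12.2.8 may not supply?** The endpoint is a count by worst grade. It does not need a grade for every result, because a lower grade in the same patient and parameter does not change the table. It does need a grade for the patient's worst value. Section 12.2.8 assigns grades to out-of-range values that are clinically relevant and is silent on the rest. The exposed patients are those whose worst out-of-range value was judged not relevant. That is more plausible for mild abnormalities than for severe ones.

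2. **Is the grader blinded?** Sections 7 and 8.1 call the trial assessor-blinded, but the grader named in 12.2.8 is the investigator, whom section 7 declares unblinded.

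3. **Do the alert values close the gap?** In part. They are numeric and the same in both arms, so they trigger review equally. They cover four haematology parameters only; Table 8 has none for chemistry or coagulation. The platelet, leukocyte and haemoglobin limits sit at the entry limits of inclusion criterion 8 (100 × 10⁹/L, 2.5 × 10⁹/L and 9.0 g/dL), so a count below the reference range but above these limits triggers nothing. After the trigger, significance is still the investigator's call.

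4. **Does the statistical section supply what 12.2.8 lacks?** No. Section 16.7 tabulates safety variables, and the list under that title in 16.6 has no laboratory-grade item. Laboratory findings other than ANA enter through adverse events, which for haematology again depend on a judgement of significance.

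5. **How large could the effect be?** Let *p* be the true share of patients with a gradable abnormality, equal in both arms, and *a* and *b* the shares of these judged relevant in arms A and B. The table shows *p·a* against *p·b*.
   - Spurious difference = *p·(a − b)*. It is zero if *a = b*, and its sign follows the sign of *a − b*.
   - Shortfall in each arm = *p·(1 − a)* and *p·(1 − b)*, present even when *a = b*. With *p* = 20% and *a = b* = 50%, both arms show 0.20 × 0.50 = 10% instead of 20%.
   - Illustration only: for *p* from 10% to 40% and *a − b* from 10 to 30 points, the difference runs from 0.10 × 0.10 = 1 point to 0.40 × 0.30 = 12 points.

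   None of *p*, *a* or *b* is in the protocol. The formula shows the mechanism and does not estimate this trial's bias.

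**The case against.** The strongest reply is that 12.2.8 is a site procedure and not an analysis rule. It does not restrict grading exclusively to relevant values, and neither it nor 4.2 says that the worst-grade table will use the investigator's grades. The numeric results come from central laboratories, so an SAP, which is not at hand, could derive grades for all of them, and nothing in the protocol forbids this. The alert values apply equally to both arms, and safety laboratory visits are scheduled in both arms through month 15. Section 16.11 makes everything outside the four hypotheses explorative, and open-label conduct is declared and justified.

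Most of this stands, and it limits the point. A reader might infer that the laboratory comparison between arms necessarily rests on unblinded judgement and is biased against AOP2014. The documents do not support that: the link from 12.2.8 to the 4.2 table is an inference, and no flagging rates are given. A reader might also infer a bias of several percentage points, but any such figure only returns the assumed flagging gap multiplied by an assumed rate.

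What the reply does not remove is that the one grading rule the protocol states is unsuited to the endpoint it states, and that 16.6 and 4.2 disagree on what the safety endpoints are. Both are matters of protocol wording, not details left for an SAP.

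**Conclusion.** The point holds as a minor one. Sections 4.2 and 16.6 do not match, and the grading rule in 12.2.8, followed as written, can leave the descriptive worst-grade table incomplete, mainly at low grades, and open to differences in judgement between arms. Size and direction cannot be derived from the protocol; equal judgement in both arms would give no spurious difference, only under-counting. The haematology alert values mitigate part of the problem. The primary endpoint and the four confirmatory hypotheses are untouched.

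This rests on one assumption: that the grades used for the 4.2 endpoint would be those assigned under 12.2.8, the only laboratory grading rule in the protocol. If an SAP already derives grades from all numeric values, what remains is to align the wording of 12.2.8 and 16.6 with it.

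**What to change.** - **12.2.8 and 16.7:** state that, for laboratory parameters with numeric CTCAE 4.03 criteria, grades are derived by program from all recorded values and reference ranges, whatever their judged relevance.
- **16.7:** tabulate worst post-baseline grade by arm, with shift from baseline. Define baseline for both arms, since the visit schedule marks a safety laboratory at the baseline visit for arm A but not for arm B, where the screening value would have to serve.
- **16.6:** add the worst-grade laboratory item so that the list matches 4.2 and the synopsis.
- **12.2.8 and 12.2.8.1:** keep the investigator's judgement of relevance or significance for deciding whether an adverse event is recorded, and for that purpose only.

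The cost is some programming and a few lines of text. No visit, sample or clinical rule changes. The sponsor should confirm that numeric values and reference ranges reach the study database, because the protocol says where the parameters are measured but does not expressly describe that transfer.

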**12.2.8.1 Hematology**

Two (2) ml of blood will be placed in an ethylene diamine tetraacetic acid (EDTA) tube and the following parameters will be measured: hemoglobin, platelet count, leukocyte count, neutrophils.

The clinical significance of each hematology value exceeding the alert values presented in Table 8 should be assessed and should be recorded in the e-CRF. When a value is clinically significant, an AE should be recorded.

**Hematology Alert Values**

| Parameter        | Alert Value                                      |
|------------------|--------------------------------------------------|
| Neutrophil count | $\leq 1.0 \times 10^9/\text{L}$                  |
| Hemoglobin       | $\leq 9.0 \text{ g/dL}$ or $5.59 \text{ mmol/L}$ |
| Leukocyte count  | $\leq 2.5 \times 10^9/\text{L}$                  |
| Platelet count   | $\leq 100 \times 10^9/\text{L}$                  |

**Table 8 Hematology Alert Values****12.2.8.2 Coagulation**

Five (5) ml of blood will be taken and placed in a citrate tube for determination of prothrombin time and activated partial thromboplastin time.

**12.2.8.3 Clinical Chemistry**

Nine (9) ml of blood will be taken and placed in a serum separation tube and the following parameters will be measured: ALT, AST, GGT, LDH, total bilirubin, AP, glucose, urea-N, creatinine kinase, creatinine, triglycerides, total protein, albumin, sodium, potassium, and calcium.

Additionally a serum pregnancy test will be performed every visit in female patients with childbearing potential and at Screening visit a serum test for Anti-HIV and a serum test for excluding active and chronic hepatitis B and C.

**12.2.9 Autoimmunity**

Four (4) ml of blood sample will be taken and placed in a serum separator tube for analysis of ANA and TSH.

#### 12.2.10 BCR-ABL measurement and genetic studies

Because of the critical importance of a timely and accurate BCR-ABL quantitation, **it is important that all PCR measurements outlined in Table 1 and Table 2 will be performed in due time and only by the indicated reference laboratories** (see Study Personnel). After inclusion, starting with the screening procedure, BCR-ABL PCR assessments will be performed centrally at the EUTOS-certified Study Reference Laboratories for PCR (BCR-ABL mRNA) in Mannheim or Jena (see Study Personnel and Table 1 and Table 2).

The total amount of blood sampling depends on the respective visit (see 12.2.12). For BCR-ABL monitoring 20-30 ml of peripheral blood will be collected at every visit. This will occur by a non-risky peripheral venous puncture. Blood sampling for BCR-ABL monitoring is an obligatory procedure and critical to determine the primary endpoint. The blood will be sent directly to the BCR-ABL reference laboratory (see Study Personnel and Table 1 and Table 2). Here, the BCR-ABL mRNA level will be quantitated after isolation of total mRNA from peripheral blood cells. Unused RNA and cDNA will be stored in a pseudonymized manner using the Patient ID. Unused RNA or cDNA from patients who agreed to take part in the translational studies (by signing additional consent form) will be stored and can be used for subsequent PCR tests or for later independent research purposes.

#### 12.2.11 Other Translational studies

At the Baseline Visit, at Visit 2, Visit 8, Visit 11 and at the EOT (Visit 13) and month 18 and 25, approximately 45 ml blood will be sampled for research purposes (see 12.2.12) if the patient has agreed to the scientific projects in a separate consent form. The donation of this additional amount of blood will not require an additional venous puncture.

Of special interest is to explore the value of 95 CD86+pDC /  $10^5$  lymphocytes at baseline (before TKI stop) as a predictor.

Serum (5 ml) will be analyzed to evaluate cytokine/chemokine profiles associated with response. The tubes will be sent by regular mail to the IMMUNE MARKER AND STEM CELL LABORATORY in Marburg (see Study Personnel and Table 1 and Table 2). Here it will be centrifuged for at least 10 minutes at about 1800 to 2000 × g. The serum will be collected, divided into 2 aliquots and stored at  $-80^{\circ}\text{C} \pm 10^{\circ}\text{C}$  until analysis. Serum samples will be diluted and assayed with antibodies specific for the respective cytokines/chemokines following standard ELISA protocols. All samples will be measured against a standard curve. All standard and experimental samples will be analyzed in duplicate. Optical density will be read on a Packard Fusion reader and the resulting values analyzed against the standard curve value using the Fusion Reader Data Analysis software. Results will be expressed as pg/ml or ng/ml.

Moreover, Heparin blood (30 ml) will be for fluorescence activated cell sorting (FACS) will be collected in collection tubes as scheduled in the Table 1 and Table 2 (see also 12.2.12). The blood samples will be shipped at room temperature by regular mail to the IMMUNE MARKER AND STEM CELL LABORATORY at the University Hospital in Marburg (see Study Personnel and Table 1 and Table 2). The frequency and activation status of pDC, monocytes, B and T cells, and other immune cell populations will be evaluated. To determine the individual response of each patient to IFN stimulation *in vitro*, cytokine and chemokine production of PBMC will be analyzed. Therefore, PBMC may be also treated with IFN for 24 hours. Incubation time was optimized for the kinetics of the different parameters.

Finally, cells from the peripheral blood will be analyzed to assess whether the response to IFN and/or IFN-typical adverse events (depression, autoimmune phenomena) can be predicted from biomarkers measured before and initiation of IFN treatment and during treatment. Such predictive potential has

been demonstrated in patients with hepatitis C or malignant melanoma, who were treated with IFN. For these studies, EDTA blood (9 to 10 ml) from the peripheral blood will be used and subjected to nucleic acid (RNA, DNA) and signal transduction (protein) analyses in the laboratory of [name] at the University Hospital of Aachen (see Study Personnel and Table 1 and Table 2). Samples will be taken before and during IFN therapy from patients in the Arm A and also those in the comparator Arm B (to control for IFN effects).

The patient can participate in the study without donating blood for those accompanying translational projects. The biomaterial sampled during this study cannot be used for commercial purpose.

### 12.2.12 Total Blood Volume to be collected from Each Patient

The total amount of blood to be taken from each patient during the study cannot be calculated because the study duration will differ for each patient. For better overview the type and volume of blood sample has been summarized in this table (Table 9).

#### Type and Volume of Blood Sampling

| Type of Sample
(Including Screening Assessments)                                                                                                                     | Volume per Sample                                     |
|-------------------------------------------------------------------------------------------------------------------------------------------------------------------------|-------------------------------------------------------|
| Safety 
 
- Hematology
 
- Coagulation
 
- Clinical chemistry
 
- ANA, TSH
 
                   | 2 ml EDTA
5 ml Citrate
9 ml Serum
4 ml Serum |
| Total                                                                                                                                                            | 20 ml                                          |
| Translational studies 
 
- Serum immune parameters
 
- FACS immune profile
 
- IFN prediction score
 
 | 5 ml Serum
30 ml Heparin
9-10 ml EDTA           |
| Total                                                                                                                                                            | 44 ml                                          |
| BCR-ABL PCR monitoring                                                                                                                                           | 20-30 ml EDTA                                  |
| Total per Screening visit                                                                                                                                        | ~ 40 ml                                        |
| Total per Baseline visit, V7 and EOT                                                                                                                             | ~ 84 ml                                        |
| Total per other visits                                                                                                                                           | ~ 36 ml                                        |

Table 9 Type and Volume of Blood Sampling

### 12.2.13 Pregnancy test

A serum or urine pregnancy test will be performed at Screening Visit and at every visit (only arm A), for women who are considered of childbearing potential. Additional urine pregnancy tests will be provided at baseline visit for usage at home in case the next study visit exceeds 28 days.

